### Recruitment, screening and informed consent procedure

Participants will be recruited by adverts distributed via the communication channels of the project partners (social media, newsletters, webpages, clinical locations, etc). Telephone and email screening will be used to identify candidate participants and to inform interested participants of the study details. An inclusion visit at the Department of Chemistry and Applied Biosciences at ETHZ will be set up for interested candidates. During the inclusion visit, participants will receive comprehensive information about the study and conditions of participation, permitting informed consent to be given. Inclusion and exclusion criteria will be assessed according to a structured interview and confirmed by a medical doctor.

### Genetic and lactose tolerance screening

For all eligible participants, a home screening test will be conducted after consent is obtained. The home screening test kit will contain lactose powder and accompanying information so that the subjects can conduct a lactose tolerance test (according to the LHBT protocol) at their home. The test will be conducted based on a standardised, previously validated questionnaire,^17^ adapted to the most recent guidelines (https://www.esnm.eu/guidelines.html)^80^,^82^ that propose the use of 25 g of lactose for lactose tolerance testing. Briefly, abdominal pain, nausea, bloating, diarrhoea, borborygmi, as well as the sum of all symptoms, will be measured on a 10-point scale with symptom intensities ranging between 0 and 9. The home screening test kit will also provide material to collect a buccal sample to determine genetic polymorphisms commonly modulating LP.

From the participants who return the buccal samples and whose polymorphism for LP is measured, 120 participants will be selected and distributed into three groups based on their LP genetic profiles and symptomatic response to the ingestion of 25 g of lactose (lactose solution).

LP volunteers experiencing symptoms will be excluded as factors other than primary hypolactasia likely explain their symptoms.

### Consent procedure

A participant’s formal written consent (online supplemental file 1) will be obtained before the participant is submitted to any study procedure. The participant is not obliged to give consent during the inclusion visit, but the screening may not take place without it. The consent form will be signed and dated by the investigator or his designee at the same time as the participant’s consent is obtained. The study participant will receive a copy of the signed informed consent, which will be retained as part of the study records.

### Study intervention

The study intervention is a carbohydrate challenge (lactose or glucose) to identify postprandial metabolomic profiles in human exhaled breath that report symptoms of LI. Participants will be assigned to one of the challenges, using stratified randomisation to ensure a balanced distribution of participants with different tolerances to lactose consumption (based on phenotype and genotype). The glucose challenge will serve as a control and enable us to consider the specificity of the Lactobreath profiles for lactose metabolism. Both challenges consist of the ingestion of the carbohydrate solution (25 g of lactose or equimolar amounts of glucose: 13 g glucose^83^) dissolved in 150 mL of water. Bias related to an expected response to consuming lactose is limited by using a double-blinded protocol for the carbohydrate intervention with a control test (glucose) to confirm the specificity of any results observed for the lactose intervention. The participants’ response will be monitored with non-invasive sampling (ie, breath and urine), wearable devices for assessment of bowel sounds and symptom assessment for 6 hours after the ingestion of the assigned carbohydrate. Intestinal gases will be monitored during the challenge by a commercially available gas-sensing capsule that will be ingested within 5 min of the ingestion of the carbohydrate solution. All experiments will be conducted at the breath analysis laboratory at the Department of Chemistry and Applied Biosciences at ETHZ.

### Study procedures

For each subject, baseline measurements will be made within 4 weeks of the intervention day which is followed by a close-out visit. The schedule of assessment table (figure 1) provides an overview of the study visits, procedures and samplings.

**Figure 1 F1:**
[figure not shown]
Overview of the planned project study protocol (screening, assessment of the baseline, intervention and completion of the study).

#### Baseline assessments

The assessment of diet and faecal microbiota will be coordinated and repeated, given the importance of obtaining robust baseline values in studies undertaking diet-microbiome analyses and the high inter-diurnal variation associated with these methods (within-person random error):^84^

Four 24-hour dietary recalls will be completed using the myfood24 online platform on four consecutive days, from days −30 to −7, before the laboratory test day.Three faecal samples will be collected by the participants at home, ideally on three consecutive days, on days +1, +2 and +3 relative to the first 24-hour dietary recall.^85^

#### Intervention day

The diet of all selected participants will be restricted for 3 days before the carbohydrate challenge test day to ensure that all FODMAPs are avoided. A standardised diet providing all meals to the participants for 3 days before the test.

On the morning of the test day, the participants will be asked to collect their first test sample, the morning urine and consume 300 mL of water at home. On arrival in the test laboratory (Department of Chemistry and Applied Biosciences at ETHZ), the participants will deliver further samples for baseline measures (figure 2):

Second urine sample.Breath for measure of exhaled H_2_ at times −30 min, −20 min and −10 min.Breath for the measure of exhaled metabolome at times −30 min, −20 min and −10 min.

**Figure 2 F2:**
[figure not shown]
Overview of the planned intervention sampling protocol at the study site. EBC, exhaled breath condensate.

The urine samples will be used for metabolomics analysis and, in the case of female participants, for a pregnancy test. Participants with a positive pregnancy test will be excluded.

All measures are indicated with respect to the start of the test (ie, the start of the consumption of the assigned carbohydrate solution), defined as t_0_.

In addition, the participants will fill out the questionnaire on LI (as used for the screening survey) at time −30 and −10 min to describe symptoms of LI before the test (baseline symptoms).

Thirty minutes before the start of the test, participants will be instructed to affix two DigeHealth wearable devices around their abdomen to record bowel sounds: one in the upper left abdominal region and another in the lower right abdominal region.

The participants will be assigned to one of the two carbohydrate challenges using stratified randomisation based on the three groups defined by the pre-screening tests. The randomisation is defined using a web-based randomisation procedure, the Clinical Trial Randomization Tool provided by the National Cancer Institute’s Division of Cancer Prevention (https://ctrandomization.cancer.gov). 100 participants will be assigned to the lactose group and asked to ingest 25 g of lactose dissolved in 150 mL of water. The remaining 20 participants (4 participants from each group 1 and 2, and 12 participants from group 3) will be assigned to the glucose group and asked to ingest equimolar amounts of glucose (13 g)^83^ dissolved in 150 mL of water. The participants and investigators will be blinded during testing to the type of carbohydrate solution assigned. Measurement bias will be addressed for all analytical platforms by measuring the samples without removing the blinding.

For each participant, the carbohydrate solution must be consumed in a time lapse of 5 min. Following the solution intake, participants will be asked to rinse their mouths with a standard quantity of water (500 mL) to avoid the detection of solution-relevant residual molecules in the oral cavity.

The participants will swallow a commercially available gas-sensing capsule (Atmo Gas Capsule) within 5 min following the lactose or glucose solution intake. The gas-sensing capsule will measure intestinal gases (hydrogen, oxygen and carbon dioxide) during its transit through the GI tract and allow calculation of the small intestinal and colonic transit times and regional gut fermentation patterns. Ingestible sensors are usually ingested with a meal to locally report on the physiological properties of the GI tract during meal processing. In this study, the gas-sensing capsule will be ingested with a carbohydrate solution, and thus it will likely not follow the same kinetics as the lactose metabolism. However, the capsule monitors gaseous profiles that provide information on its GI localisation and the production of lactose-derived H_2_ by the colon processes over several hours after its ingestion; thus, a definition of the time window during which the gas-sensing capsule will report on lactose processing will be possible. Preprandial and postprandial samples will be collected at predefined times as indicated in figure 2.

To normalise participants’ hydration, particularly to facilitate urine collection, they will be offered a standardised quantity of water based on their body weight to be consumed in regular portions during the post-ingestion period. No other foods or fluids will be permitted during the 6-hour postprandial testing.

After the 6-hour sampling, the participants will be given a standardised meal at the laboratory. Following this meal, they may drink still water ad libitum but will refrain from eating other foods until the final symptoms assessment 9 hours after the intervention.

Intestinal excretion of the gas-sensing capsule will mark the end of the intervention. This will be confirmed by participant verification of the mobile phone app each bowel movement to check if: (a) the temperature has dropped below 33°C and/or (b) the data transmission after flushing away the faeces is lost. In the time following the carbohydrate challenge and before excretion is confirmed, the participant can resume their everyday life while always keeping the capsule receiver within 2 m of their body. The participant should avoid strenuous exercise before the capsule is excreted. Before the confirmed excretion of the capsule, participants must not undergo an MRI examination unless an X-ray is performed to confirm that the capsule has left the body. If the excretion of the capsule is not confirmed, the recommended Capsule Retention Procedure, defined for the use of Atmo Gas Capsule in previous clinical trials, will be implemented by the team with the gastroenterology team of UHZ. The bowel sound wearable devices should be kept on for 9 hours after the beginning of the test until the final symptoms assessment 9 hours after the intervention.

Additional subjects will be recruited from the pool of participants to the survey should the number of participants completing the lactose and glucose tests fall below the targeted numbers. It should be noted that although symptoms of small intestinal bacterial overgrowth might be experienced by some participants after glucose ingestion,^85^ the acute nature of the study design renders this possibility unlikely. These participants will be retained for the data analysis, and their parameters, including the GI symptoms, will be analysed in light of the composition of their faecal microbiota.

### Sample collection

During the baseline period, all participants will collect and send by post stool samples for genomic characterisation of the gut microbiota. Faecal samples will be stored at −80°C. They will be analysed using shallow shotgun sequencing for a mechanistic understanding of the microbial features associated with lactose metabolism.

Breath and urine will be sampled on the intervention day, both before and during the 6 hours following the consumption of the assigned test drink. Breath sampling will be performed using a secondary electrospray ionisation source coupled to a high-resolution mass spectrometry system for direct and real-time detection of VOCs and using an H_2_ breath solid-state sensor for detection of exhaled hydrogen. Standardised breath sampling protocols will be developed for precise measurements of biomarkers of dietary intake and metabolism.

In addition, exhaled breath condensate (EBC) samples will be collected using a glass cold trap cooled to −78°C using a mixture of isopropanol. To collect EBC samples, participants exhale through the spirometry filter and a short-length tube, and their exhaled breath condenses in the cold trap. Blank samples will also be obtained by flushing 2 mL of water through the tubing and freezing it in the cold trap. All EBC samples will be stored at −80°C at the premises of ETHZ until thawed for subsequent analysis. Participants will be provided with the needed breath delivery equipment (ie, mouthpiece) and asked to breathe normally for up to twelve times per sample (this includes baseline measurements). Breath samples will be collected before the intervention and at nine time points following the intervention (15 min, 30 min, 60 min, 90 min, 120 min, 180 min, 240 min, 300 min and 360 min). Participants will be asked to provide four urine samples (two baseline samples before the intervention and two sample pools collected during the intervention (0–180 min and 180–360 min). Samples will be stored at 4°C during the test and before further analysis, all urine samples will be stored at −80°C at ETHZ.

### Safety

The main risk presented by the study intervention (ingestion of lactose solution) is minor GI symptoms (eg, abdominal discomfort) due to LM, and does not differ from the widely used LI diagnostic protocol, the LHBT. There is a potential risk associated with the use of a gas-sensing capsule for the investigation: the failure of the capsule to be excreted. A protocol is in place for this very unlikely eventuality that will be implemented under the guidance of the study Principal Investigator (PI) and a specialist gastroenterology team of the University Hospital Zurich. No cases of capsule retention have been reported for the Atmo Gas Capsule across the various clinical trials conducted for the product to date. The risks of the intervention are outweighed by the potential benefits of the study for improving clinical diagnosis of food intolerances (improved specificity of food intolerance diagnosis using non-invasive breath measurements) and offering mechanistic insights into the symptoms associated with LM. No severe adverse reactions are anticipated, but the Monitoring Committee will check for these.

### Analysis of samples

#### Real-time breath measurements (breath metabolome)

On-line chemical analysis of exhaled breath will be carried out by ETHZ using a SESI source purchased from Fossil Ion Technology SL, coupled with an HR-MS system (Q Exactive Orbitrap, ThermoFisher Scientific). SESI-MS is a well-established and robust analytical technology specially developed for in-depth breath characterisation. Its applicability has already been demonstrated in clinical studies previously published by ETHZ.^70^,^77^ The real-time approach of this method is practical for the high sampling frequency planned for the study and has already been shown to be sensitive to acute dietary intervention.^78^

By conducting breath analysis during the 6 hours following the intervention, it will be possible to follow multiple features over time and to obtain a major part of the postprandial kinetic profile of the participants. During a real-time breath measurement using SESI-MS, the participant exhales through a disposable antibacterial mouthpiece and a short-length heated sample transfer line into the ionisation chamber. In the SESI chamber, a mist of charged droplets interacts with breath molecules for charge transfer and ionisation. The produced charged breath molecules are then introduced into the mass analyser for mass-to-charge (m/z) separation and detection. Measurements are carried out in the positive and negative ion mode that facilitates the determination of protonated and deprotonated species, respectively. Exhaled CO_2_, pressure, flow rate and breath volume are simultaneously recorded using an interface (EXHALION) connected at the front-end part of the sample transfer line. Mass calibration and tuning of the system in both ionisation modes are performed once per week or more often if required. The stability of the whole system is monitored daily by introducing gaseous standards (eg, acetone) at known concentrations using a gas standard generation system that additionally allows quantification calculations of target metabolites.

##### Identification of metabolites

A strategic feature of the Orbitrap is the ability to obtain tandem mass spectra (MS2) for selected ions through collision-induced dissociation. This feature significantly enhances the instrument’s chemical specificity, enabling the distinction between isomers, which is crucial for molecular identification and quantification. EBC, also collected during online breath sampling for each participant, will be analysed using standardised liquid chromatography-mass spectrometry (LC-MS) methods (reversed-phase and HILIC) and GC-MS for comprehensive metabolite coverage and chemical identification using spectral libraries.

##### Quantification of breath metabolites

Quantification of selected exhaled breath metabolites of interest is of major importance. Currently, SESI-MS is semi-quantitative and quantification is only possible for the metabolites for which the calibration curves can be obtained. Thus, to quantify detected exhaled breath metabolites, we will use a range of built-in-house or commercial systems for the controllable generation of gaseous standards in a chemical environment simulating human exhaled breath. By generating calibration curves of detected metabolites of interest using reference material, we can provide quantitative information for these specific metabolites. We can already quantify SCFAs in the gas phase (in the range of low ppt to high ppm), which are key bioactive components in the gut produced by dietary components, and the metabolism of lactose by the colon in lactose malabsorbers by colonic fermentation.^86^ This will complement the mechanistic analysis of the H_2_ breath test.

### EBC sample analysis

EBC samples will be analysed via dynamic headspace vacuum transfer in-trap extraction gas chromatography-mass spectrometry and LC-MS. GC-MS will use an Agilent 7890B GC coupled to a 5977A mass detector with an Optima 5 MS Accent column (25 m×250 µm×0.25 µm) and helium carrier gas. Column temperature starts at 35°C for 3 min, rising to 300°C at 5 °C/min over 60 min, at 0.8 mL/min flow. Electron impact spectra are collected from m/z 30–350 at 230°C. LC-MS analysis employs an Acquity UPLC system coupled with a Q-Exactive mass spectrometer. Reverse-phase separation uses BEH C18 columns (2.1 mm×150 mm, 1.7 µm) at 30°C, while hydrophilic separation uses BEH Amide columns (2.1 mm×150 mm, 1.7 µm) at 45°C, both with respective pre-columns.

### Hydrogen breath test

Exhaled breath H_2_ will be measured using a non-invasive hydrogen gas microanalyser (QuinTron BreathTracker Digital Microlyzer, model SC; QuinTron Instrument Company, Milwaukee, Wisconsin, USA). The BreathTracker has a resolution of 1 ppm H_2_ and a linear detection range between 2 and 150 ppm H_2_ with an accuracy of ±2%. It also features a two-step calibration and a purging mode that eliminates cross-interference (inter-subject contamination) and provides a stable internal baseline. The gas analyser will also be calibrated externally using a known-concentration H_2_ compressed gas standard. Breath samples (30 mL each) will be insufflated in the Breath Tracker and will be collected as CO_2_-corrected H_2_, expressed in parts per million (ppm). The maximum increase in breath H_2_ will be calculated by subtracting baseline H_2_ values from the highest H_2_ value post-lactose ingestion based on the BreathTracker readings. An increase of at least 20 ppm hydrogen between any two time points after 30 min in the study will indicate LM.^80 87^

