### Statistical analysis

#### Primary endpoint

Supervised machine learning algorithms (such as random forest and partial least squares discriminant analysis) will be applied based on Zheng *et al*^100^ and will identify molecular breath profiles that discriminate different clinical traits associated with LM based on the levels of metabolites in the exhaled breath after the intake of lactose. Models will be created to explore separately the breath profiles that are discriminated for each trait of LM, including the response to the LHBT, polymorphisms for LP, lactose-derived metabolites in urine and the GI symptoms of LI taken individually and collectively. To reduce overfitting and deliver reliable estimates of the models, we will apply machine learning with voting, a strategy for classification based on selecting the output with the most classes. Clinical traits will be modelled as either categorical variables, continuous variables or both, where appropriate. This analysis will be conducted first on a subset of 50% of the recruited participants to allow the most predictive metabolites to be identified within the timeframe of the study. The subset will be balanced to represent the three test groups. The same analysis workflow will later be applied to the whole cohort, with 20 participants (stratified for group) removed from all modelling to allow for internal validation of the models. The best profiles (Lactobreath profiles) that associate the breath exhalome with each of the clinical traits of LM will be tested in the 20 remaining participants to assess their validity. Further, to consider the specificity of the Lactobreath profiles for lactose metabolism, the profiles will be evaluated in the participants assigned to the glucose test with additional comparisons between intervention types (glucose vs lactose) across all three participant groups. The molecular profiles with the best performance for predicting LM clinical traits will be retained to determine the identity and quantification of the molecules composing the selected profiles.

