The diagnostic performance of the lactose-induced breath profiles identified for the clinical traits will be assessed using the following parameters: sensitivity, specificity, positive predictive value, negative predictive value, the likelihood ratio of a positive test, likelihood ratio of a negative test as described by Beyerlein *et al*^17^ and Jellema *et al*.^81^ For each parameter, the novel breath profiles will be compared with the reference diagnostic tool. The participants are grouped by LHBT and genetic test results as these are commonly used in clinical practice for LI diagnosis and are, therefore, suitable for evaluating the performance of the breath biomarkers. The level of significance will be two-sided (α=0.05). Corrections for multiple testing will be made using the false discovery rate.^101^

Analysis populations: the analysis populations are defined by the criteria used to select the three study groups and the two assigned carbohydrate interventions, resulting in six groups for analysis.

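### The binary hydrogen-breath label for lactose malabsorption is set by a quantity that, read literally, ignores the baseline used for the continuous measure, so the two LHBT traits can disagree for the same participant

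*Protocol article*

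**What the plan says.** Two consecutive statements in the Hydrogen breath test section of the protocol article define two quantities.

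- Continuous measure: "The maximum increase in breath H_2_ will be calculated by subtracting baseline H_2_ values from the highest H_2_ value post-lactose ingestion". No threshold is attached.
- Binary label: "An increase of at least 20 ppm hydrogen between any two time points after 30 min in the study will indicate LM". Baseline is not mentioned.

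The sampling times come from three other places.

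- Intervention day: "Breath for measure of exhaled H_2_ at times −30 min, −20 min and −10 min".
- Text below Figure 2: "All measures are indicated with respect to the start of the test", which is the start of drinking the assigned solution. All three baseline samples therefore precede time zero.
- Sample collection: "nine time points following the intervention (15 min, 30 min, 60 min, 90 min, 120 min, 180 min, 240 min, 300 min and 360 min").

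The label is used under Statistical analysis, Primary endpoint: "Models will be created to explore separately the breath profiles that are discriminated for each trait of LM, including the response to the LHBT". That section allows a trait to be modelled as categorical, continuous or both. On diagnostic accuracy it adds: "For each parameter, the novel breath profiles will be compared with the reference diagnostic tool". It names the LHBT and the genetic test as suitable for evaluating the breath biomarkers.

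**The concern.** The 20 ppm cut is not tied to the increase that has just been defined. If both points must lie after 30 min, no baseline value can be one of them. The label then measures how far hydrogen climbs within the window from 60 to 360 min, while the continuous measure asks how far it climbs above fasting. These are different questions and can have different answers.

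The LHBT response is one of the modelled traits and one of the tools the new breath profiles are benchmarked against. If its continuous and binary versions conflict, the LHBT-trait models and the accuracy figures set against the LHBT depend on which version was used. The validation set is 20 participants, so even a few changed labels would be visible there.

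**Working it through.** The plan states no error rate or sample size for this rule, so there is no figure to reproduce. The check applies both definitions to the protocol's own sampling times. The H2 curves and noise SDs are assumptions, because the document gives none.

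**Eligible samples.** Of the nine post-dose samples, seven fall strictly after 30 min: 60, 90, 120, 180, 240, 300 and 360. Ordered pairs: 7 × 6 / 2 = 21. If the 30 min sample counts, there are eight samples and 8 × 7 / 2 = 28 pairs.

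**Readings of the label rule.**
- A: both points strictly after 30 min (literal).
- B: the 30 min sample also counts.
- C: only the later point must be after 30 min, so baseline may be the first point.

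Under each reading, the any-two rise is the largest value of (later − earlier). The comparator is highest post-dose value − baseline.

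**Illustrative curves (ppm at 15, 30, 60, 90, 120, 180, 240, 300, 360 min).**

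Curve 1, baseline 5: 5, 14, 30, 36, 38, 36, 34, 30, 26.
Curve 2, baseline 25: 25, 22, 16, 10, 6, 6, 12, 20, 27.

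| Quantity | Curve 1 | Curve 2 |
|---|---|---|
| Rise over baseline | 38 − 5 = 33 | 27 − 25 = 2 |
| Any-two, reading A | 38 − 30 = 8, negative | 27 − 6 = 21, positive |
| Any-two, reading B | 38 − 14 = 24, positive | 21, positive |
| Any-two, reading C | 38 − 5 = 33, positive | 21, positive |

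The early-rise discrepancy depends on the reading; the dip-and-return discrepancy does not.

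**Which early risers are affected.** With a linear rise to a plateau and reading A:
- Plateau reached by 60 min: the label is negative for every total rise tried (25, 40 and 60 ppm).
- Onset at 30 or 45 min and plateau at 90 to 120 min: negative only for the 25 ppm rise.
- Onset at 60 min: never negative.

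A curve that reaches 45 ppm at 60 min and goes on to 70 ppm gains 25 ppm and stays positive under every reading.

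**Chance positives.** For independent noise with SD σ, the difference between two single samples has SD √2 × σ = 1.41σ. One sample minus the mean of three baselines has SD √(1 + 1/3) × σ = 1.15σ. Reading A also takes the largest of 21 such differences, against seven for a baseline rule on the same samples. Both features raise the chance of a spurious 20 ppm rise under the any-two rule.

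Simulation: 200,000 flat curves per SD, mean 12 ppm, values truncated at 0.

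| Assumed SD | Any-two (A) | Baseline rule, samples after 30 min | Baseline rule, all nine samples |
|---|---|---|---|
| 4 ppm | 0.3% | 0.0% | 0.0% |
| 6 ppm | 11% | 1.2% | 1.5% |
| 8 ppm | 33% | 8.0% | 10% |

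The direction follows from the structure of the rule. The size depends on the SD.

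**The case against.** The strongest reply has five parts.

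- **Only one statement carries a threshold.** The maximum increase is a continuous quantity, and the plan allows categorical and continuous versions of a trait side by side. This stands: the document does not issue two conflicting labels. It leaves the two versions of one trait unlinked.
- **Nothing declares rise over baseline to be true LM status.** A reader might infer that the rule mislabels participants. The document does not support that. The rule carries two citations that cannot be checked here, and a late rise from 6 to 27 ppm after lactose, with no other food allowed, is compatible with colonic fermentation. What can be shown is disagreement between two stated quantities, not error against a known truth.
- **The early-riser case turns on the reading.** This stands. It disappears for Curve 1 if the 30 min sample counts, and altogether if baseline may be the first point. Nor do all early risers become negative. But a label that changes with an unstated convention is itself a fault in the rule, and the dip-and-return case survives every reading.
- **The noise figures are assumed.** This stands. An SD of 6 to 8 ppm around 12 ppm is 50% to 67% of the mean. At 4 ppm the difference is negligible. Curve 2 also needs a fasting level of 25 ppm despite three days of FODMAP-avoiding meals, and the document does not say how often that occurs.
- **The reach is limited.** The primary objective concerns GI symptoms, and the groups and randomisation strata come from genotype and screening symptoms. This stands. The Primary endpoint text does speak of participants grouped by LHBT, but the eligibility, screening and randomisation text does not use this rule, so a reader should not infer that it drives allocation.

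**Conclusion.** The point holds in limited form. The label rule, read literally, makes no use of the three baseline samples, although the statement before it subtracts them. The continuous and binary LHBT traits can therefore disagree in both directions: +33 ppm over baseline but negative (reading A only), and +2 ppm over baseline but positive (all readings).

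The any-two rule is structurally more prone to chance positives. The illustrative excess runs from 0.3% against 0% at an SD of 4 ppm to 11% against about 1% at 6 ppm. These are not estimates for this trial: they rest on flat curves, independent noise and assumed SDs.

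The LHBT-trait model and the LHBT benchmark comparison are affected; the study groups and the randomisation are not. How many participants would change label cannot be computed from the document. All H2 samples are collected whichever definition is used, so nothing is lost if the rule is settled before labels are generated.

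**What to change.** Reconcile the two statements before any LHBT label is generated, so that one definition feeds both the continuous and the binary trait. The natural choice keeps the existing 20 ppm threshold and applies it to the baseline-subtracted increase already computed. State:

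- how the −30, −20 and −10 min values are combined, for example as their mean;
- whether the 30 min sample counts;
- that the same post-dose samples are used for both versions of the trait.

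If the cited sources support the any-two rule, report it as a sensitivity analysis, with the number of participants whose label differs.

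Cost: one sentence in the plan and a small amount of extra analysis. No new data are needed.
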